# 4. Study Population

## 4.1 Sample Size

68 women in total, 17 participants per study group

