5.5.2 Treatment allocation

Randomization will be into one of four study groups:

High Frequency – Manual stimulation: Women randomly allocated to this group will receive 3 acupuncture treatments in the 7 days prior to menses and 1 acupuncture treatment in the first 3 days of menses. Stimulation will be provided by manual acupuncture, achieving DeQi upon needle insertion. Subsequent stimulation based on practitioners differential diagnosis. Needles will be retained for 20-30 minutes

High Frequency – Electro acupuncture stimulation: Women randomly allocated to this group will receive 3 acupuncture treatments in the 7 days prior to menses and 1 acupuncture treatment in the first 3 days of menses. Stimulation will be provided by Electro-Acupuncture, achieving DeQi upon needle insertion. Subsequent stimulation will be using a 2/100Hz waveform for 20-30 minutes.

Low Frequency – Manual Stimulation: Women randomly allocated to this group will receive 3 acupuncture treatments in the 3 weeks prior to menses (1/week) and 1 acupuncture treatment in the first 3 days of menses. Stimulation will be provided by manual acupuncture, achieving DeQi upon needle insertion. Subsequent stimulation based on practitioners differential diagnosis.Needles will be retained for 20-30 minutes

Low Frequency – Electro acupuncture stimulation: Women randomly allocated to this group will receive 3 acupuncture treatments in the 3 weeks prior to menses (1/week) and 1 acupuncture treatment in the first 3 days of menses. Stimulation will be provided by Electro-Acupuncture, achieving DeQi upon needle insertion.Subsequent stimulation will be using a 2/100Hz waveform for 20-30 minutes.

5.5.3: Withdrawal procedures

If a participant wishes to withdraw from the trial they will be immediately removed from treatment. The most recent menstrual pain diary will be used and they will be requested to complete an SF-36.

If a participant withdraws during intervention they will not be replaced however if they withdraw post randomization but prior to the first treatment they will be replaced.

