## 7.2 Study assessments

The menstrual pain diary will be used to assess primary and secondary endpoints at baseline and at the end of every menstrual period during the 3 month study period. Follow-up pain diaries will also be collected at 1, 6 and 12 months post trial completion.

The SF-36 will be assessed at baseline and then at 1 month post trial completion.

Patient satisfaction with the trial will be assessed at the end of the trial with an exit questionnaire given after the final acupuncture treatment.

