# 9. Statistics and Data Analysis

## 9.1 Sample Size calculation:

This trial is designed to demonstrate a 20% difference in average pain intensity between groups as measured by the Numeric Rating Scale (NRS). Based on previous study data (65) a standard deviation of 1.3 units on a pain scale was used. An alpha of .05 and power of 90% gives a total sample size of 60 women. Previous studies (35,65) have had relatively low loss to follow-up (~10%) therefore a sample size of 68 women will be used to account for the predicted loss to follow-up of 10%.

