## 9.2 Proposed Analysis:

For the data from the clinical trial a range of data analysis techniques will be undertaken including simple descriptive statistics; two way repeated measures ANOVA for NRS pain scores and SF-36 scores. Regression analysis with GLM will be used to examine factors influencing NRS scores, analgesic intake, secondary symptoms and non-pharmacological therapies. Non-parametric data such as analgesic intake, presence of secondary symptoms and usage of non-pharmacological therapies will be analysed by Mann-Whitney U-test.

Data from the in-depth interviews will be transcribed verbatim from the digital recording by the researcher. NVIVO will be used to manage the transcribed data and digital recordings. Thematic analysis will be used to identify emergent themes from the data.

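### The repeated measures ANOVA named for pain, in its classical form, drops a woman who misses one diary, a case that neither the withdrawal rule nor the 10% allowance covers

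*Protocol*

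**What the plan says.** Section 9.2 of the protocol fixes the method for pain: "two way repeated measures ANOVA for NRS pain scores and SF-36 scores". It does not say which diaries enter the ANOVA or what happens to a woman with a gap in her series.

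Section 7.2 takes diaries at baseline and after each menstrual period of the three-month treatment phase. It adds: "Follow-up pain diaries will also be collected at 1, 6 and 12 months post trial completion".

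The only rule for incomplete data is in 5.5.3, for a woman who withdraws: "The most recent menstrual pain diary will be used and they will be requested to complete an SF-36".

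The sample size is set in 9.1: "An alpha of .05 and power of 90% gives a total sample size of 60 women". The increase from 60 has a single stated purpose: "a sample size of 68 women will be used to account for the predicted loss to follow-up of 10" (per cent). Section 4.1 gives the split: "68 women in total, 17 participants per study group".

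**The concern.** A classical repeated measures ANOVA works on a rectangular table with one row per woman and one column per time point. A row with an empty cell is normally deleted whole. A woman who attends throughout but loses or skips one cycle's diary would then contribute nothing, although her other diaries were observed.

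No provision in the protocol reaches her. She has not withdrawn, so 5.5.3 does not apply, and she is not lost to follow-up, so the 10% allowance was not set aside for her.

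Two things are at stake. The first is waste of primary-outcome data in a trial with 17 women per group. The second is selection: the analysed set becomes the women with perfect diary returns. Section 5.5.2 gives the high-frequency groups three treatments in the seven days before menses and the low-frequency groups one a week for three weeks. If diary compliance follows visit schedule, deletion would act unevenly on one of the two factors under test. That is a risk and has not been demonstrated.

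**Working it through.** **Inputs from the protocol.** Target 60 women, power 90%, alpha 0.05, SD 1.3, 10% loss, 68 randomised in four groups of 17 (4.1 and 9.1). Three treated-cycle diaries after baseline (7.2). The baseline diary is required for entry (5.3), so it is taken as never missing.

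**Inputs assumed.** A missed-diary rate *m*, the same for each diary and independent between diaries. The protocol gives none, so a range is shown.

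**Step 1: the plan's own figure.** 60 / 0.9 = 66.7, so 67. By group, 15 / 0.9 = 16.7, so 17, and 4 × 17 = 68. The 68 reproduces. After the planned loss, 68 × 0.9 = 61.2 women remain, about one more than the target.

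**Step 2: women with complete sets.** Formula: starting number × (1 − *m*)³.

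| Missed per diary | Start 68 (withdrawn women kept) | Start 61.2 (after 10% loss) |
|---|---|---|
| 1% | 66.0 | 59.4 |
| 2% | 64.0 | 57.6 |
| 5% | 58.3 | 52.5 |
| 10% | 49.6 | 44.6 |

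**Step 3: rate at which the number falls below 60.** Solve start × (1 − *m*)³ = 60.

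- Start 61.2: *m* = 1 − (60/61.2)^(1/3) = 0.7%.
- Start 68: *m* = 1 − (60/68)^(1/3) = 4.1%.

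The second line is the favourable reading, in which the last-diary rule keeps every withdrawn woman in the analysis.

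**Step 4: does power fall with the headcount?** Section 9.1 aims at a 20% difference but does not give the mean it refers to. A difference of 1.11 NRS units is therefore assumed. With SD 1.3 and two halves of the trial compared, it gives the stated 90% at 60 women. Power is from the noncentral t distribution, two-sided.

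For a single diary the SD is 1.3. For a mean of three diaries with correlation *r* it is 1.3 × √((1 + 2*r*)/3), which is 1.06 at *r* = 0.5 and 1.16 at *r* = 0.7. Both correlations are assumptions.

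| Women analysed | One diary | Mean of three, *r* = 0.7 | Mean of three, *r* = 0.5 |
|---|---|---|---|
| 60 | 90% | 95% | 98% |
| 53 | 86% | 93% | 96% |
| 45 | 80% | 88% | 93% |

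The one-diary column does not describe the method named in 9.2, which uses several diaries per woman. With three diaries averaged, power stays close to or above the planned 90% even at 45 women.

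**The case against.** The strongest reply is that 9.2 names a family of methods in one clause. It does not mention complete cases or listwise deletion, and a statistical analysis plan could say how a skipped diary is treated. That stands as a limit: deletion is a property of the method as normally run, and the protocol does not state it. It does not remove the point, because the method itself is fixed in the protocol and another method would not raise the difficulty.

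The missed-diary rates are also assumed, and several features favour return. The investigator collects outcomes after each period (section 8), every group has a treatment in the first three days of menses (5.5.2), the NRS was chosen partly for compliance (section 8), and compliance is reviewed regularly (10.1). If withdrawn women are kept through the last-diary rule, a 2% missed rate still leaves 64 women.

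A reader might infer three stronger claims, none of which the protocol supports:

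- **Power falls to 80%.** That figure treats the outcome as one measurement per woman. Averaging several diaries offsets much of the loss.
- **All six post-baseline diaries must be complete.** The protocol collects those at 6 and 12 months but does not say that they enter the ANOVA.
- **The tests are too liberal for want of sphericity.** The assumption bears only on the time and group-by-time tests and leaves the between-group main effects untouched. Nothing says that a correction would be omitted.

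**Conclusion.** The point holds as a weakness in the chosen method, and the plan should be changed. In its classical form the ANOVA named in 9.2 discards the observed diaries of any woman with one gap, and no stated rule or allowance covers her.

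On the planned 10% loss, the margin over 60 is about one woman and is used up once 0.7% of each treated-cycle diary is missed. If withdrawn women are kept, the figure is 4.1%. At an assumed 5%, complete sets number about 58 of 68, or 52 to 53 after the planned loss.

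These counts rest on deletion of incomplete sets, on three diaries entering the model and on independent misses at an assumed rate. The consequence is lost primary-outcome data and possible selection by compliance. A material loss of power has not been shown.

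**What to change.** In 9.2, replace the ANOVA for NRS pain with a likelihood-based linear mixed model for repeated measures. Its terms should include baseline pain and the two randomised factors, frequency and stimulation, with an unstructured covariance over the three treated cycles. State that it uses every returned diary and includes any woman with at least one post-randomisation diary. Keep the 6- and 12-month diaries out of the treated-cycle model, so that a missing late diary cannot remove treated-cycle data.

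In 5.5.3, state that a withdrawn woman's observed diaries enter this model as they stand and that her last diary is not carried forward. Otherwise the two sections would conflict. This concerns only how the data are analysed.

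The cost is wording in two sections and standard software, with no extra visits, women or data. The downside is that the model assumes diaries are missing at random, but this is weaker than what a complete-case ANOVA assumes. The unstructured covariance also removes the sphericity assumption for the time and group-by-time tests.

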# 10. Monitoring and quality assurance

## 10.1 Project management and trial management group

The primary investigator, [name], will have regular meetings with his supervisory panel and will discuss recruitment, compliance, retention and follow up as well as the implementation of the overall trial protocol. These meetings will also discuss any adverse event data reported by study acupuncturists.

[name] will also have regular email/phone conversations with other study acupuncturists to discuss any issues with recruitment, compliance, retention and follow up as well as the implementation of the overall trial protocol. In addition to this quality control will be undertaken at several points during the trial with each study acupuncturist being assessed at least once. Prior to the implementation of the protocol all study acupuncturists will be trained by the Primary Investigator and the AcuSensor device will be used to standardize needling technique to ensure that similar quality of stimulation is delivered by all study acupuncturists.

There is no data monitoring committee for this study.

# 11. Good Clinical Practice Module

## 11.1 Ethical conduct of the study

The research has been submitted to both the UWS Human Research Ethics committee and the HDEC for approval.

## 11.2 Investigator responsibilities

11.2.1 Informed consent

All participants will be required to give informed consent prior to being issued with the menstrual pain diary. Informed consent will be undertaken either face to face with [name] or via post.

11.2.2 Emergency contact with Investigators

All participants will be given emergency contact numbers of both the study acupuncturists and the primary investigator [name]

11.2.3 Investigator indemnification

Following ethical approval, clinical trial insurance will be registered with the University

11.2.5 Data Recording

All data will be entered electronically into a secure database with offsite backups at Centre for Complementary Medicine Research at The University of Western Sydney

11.2.6 Confidentiality

All data is confidential. All study participants will be allocated a Study ID

11.2.7 Data protection

All electronic files will be password protected. All paper files will be kept in locked filing cabinets at the home of the primary investigator, [name]

# 12. Reporting, Publication and Notification of Results

## 12.1 Authorship policy

The Primary investigator and supervisory panel will be authors of the main manuscript.

## 12.2 Publication

The study results will form part of the primary investigators PhD thesis. In addition these results will be presented at conferences and published in appropriate journals.

